### 2.5. Blinding

This will be a single-blinded trial. Baseline and post-intervention measurements and measurement assessments will be performed by an evaluator who is blind to the group. The statistician performing the statistical analysis will also be blinded to the allocation and treatment of groups. Due to the nature of exercise interventions, it will not be possible to blind the participants.

### 2.6. Intervention Protocol

#### 2.6.1. Experimental Group

The hamstring stretching exercise program will be conducted five times a week, 20 min per session, for 8 weeks. The exercise program will be supervised by an experienced physiotherapist (5 years of clinical experience).

The intervention will be divided into two parts. The first part will include rolling with a foam roller [23]. For the roller massage, the participants will have to sit on a mat with a roller placed under the leg (Table 1). The participants will have to move up and down to massage their thighs between the buttocks and the knee. The roller massage will be performed for 5 min. The second part will include active hamstring stretching combined with hip flexion mobilization and the maintenance of correct hip flexion, protecting the lower spine. The exercise protocol will include three exercises (Table 1). The session will consist of 3 sets of each exercise. All positions will be maintained for 30 s with 30 s of relaxation [24]. The level of difficulty (level of hip flexion) will be self-regulated by the participant based on their physical condition and discomfort [25]. Equipment used in the active hamstring flexibility exercises program will consist of a massage foam roller and a gym mat.

In the experimental intervention, the exercise program will be based on participant education, home-based individual exercises, and regular group meetings for check-ups by a physiotherapist according to a preset schedule.

The first week of the intervention will consist of 4 full days of participant education and home exercise instruction. Sessions will be supplemented with information about the anatomy of the lower spine and advice, including postural instructions and practical demonstrations of lifting, pushing, pulling, and other daily actions. Other weeks of the intervention will be dedicated to individually prescribed home exercises. 

The first check-up with the physiotherapist will take place 2 weeks after the start of the exercise program, to check that the participant is performing the exercises with the correct execution and regularity. The next check-up with the physiotherapist will take place 4 weeks after the start of the exercise program when the physiotherapist will re-check the exercises. The participants will record their exercise frequency on a pre-prepared diary-record sheet. 

#### 2.6.2. Control Group

Students assigned to the control group will receive an educational booklet containing information on the causes of low back pain, the anatomy of the spine and its relation to the muscular chain, and tips for spinal care during daily life activities. The control group will be encouraged to perform their regular baseline activities without the addition of a specific lower extremity flexibility program. Participants will also be contacted weekly by email and/or telephone. Participants will be asked to continue their daily routine and receive neither physical therapy treatment programs nor other medical care.

The control group participants will be advised to take part in the same hamstring stretching training as the intervention group in the evaluation session after the study is completed.

### 2.7. Assessment

Participants who fulfill the eligibility criteria, agree to participate, and sign a written informed consent form will be included in the study subject to the assessment. A blinded assessor-physiotherapist with five years of clinical experience will check the qualifying criteria. A baseline assessment will be conducted before participants are randomly assigned to groups. An outcome assessment will be collected at the start of the study and immediately after the 8-week intervention.

### 2.8. Pre-Intervention Data Collection Sheet 

Before random group assignment, participants will receive the survey containing questions about age, gender, current physical activity (number of training days and hours per week, sports discipline), history of illnesses, injuries, surgeries due to spinal ailments, LBP physiotherapy and confirmed by which medical doctor, and body posture defects. A questionnaire will also be used to collect data about the experience of LBP within the last three months. Individuals who respond positively (“yes”) to the question “Have you experienced low back pain for the last three months?” will answer the question on the frequency of LBP (rarely, a few times per week, often, or constantly) and the types of situations in which LBP occurred, increased, or worsened.

### 2.9. Outcome Measures

Primary outcome measures (average pain intensity, functional disability, perceived musculoskeletal discomfort during prolonged sitting) will be collected at baseline and immediately after the 8-week intervention, and the global perceived improvement will be assessed immediately after the 8-week intervention. The secondary outcome measure (flexibility of the hamstring) will be collected after the 8-week intervention. Table 2 shows the distribution of the different measures across the timepoints during the study.

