## Abstract

Participants will be recruited from the Faculty of Physical Education and randomly assigned to either the hamstring stretching group or the control group with education only. The primary outcome measures will be pain intensity, musculoskeletal discomfort, and functional disability. Secondary outcome measures will be satisfaction with the intervention and flexibility of the hamstring. A total of 44 participants fulfilling the inclusion criteria will complete the study. As an increase in LBP frequency is observed, it seems justified to determine effective interventions for LBP and musculoskeletal discomfort in young people. The findings of this study will provide information about the effect of an 8-week intervention involving active hamstring flexibility exercises with hip flexion mobilization on the reduction of LBP and musculoskeletal discomfort during prolonged sitting in young adults. We hope this study will add to the development of ergonomic recommendations for young people with LBP.

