### 2.10. Primary Outcome Measures

Pain intensity

The Visual Analog Scale (VAS) will be used to assess average pain intensity graded from 0 (no pain) to 10 (unbearable pain). Mild pain or no pain will be defined as VAS 0–3, moderate pain as VAS 4–6, and severe pain as VAS 7–10 [26]. Participants will be asked to rate their maximum pain intensity from the last 3 months.

2.Functional disability

The Revised Oswestry Low Back Pain Disability Index (ODI) will be used to assess the level of functional disability resulting from LBP. The questionnaire consists of 10 items related to different aspects of function regarding activities of daily living. Each item will be scored from 0 to 5, with higher values representing greater disability. The total score will be multiplied by 2 and expressed as a percentage [27].

3.Perceived musculoskeletal discomfort during prolonged sitting

The Borg CR-10 scale will be used to assess perceived musculoskeletal discomfort during 1 h of sitting, classified as prolonged sitting. The Borg CR-10 scale is presented in such a way that test subjects can indicate in which parts of the body they feel discomfort (i.e., neck, shoulder, upper back, lower back, hip/thigh, and knee) and the degree of discomfort they feel (on a scale from 0 to 10, 0 being no discomfort and 10 being extremely uncomfortable) [28]. The scale and body chart will be determined according to a standardized Nordic questionnaire [29]. During university classes, the participants will be required to spend an hour sitting in a chair with a backrest. The initial sitting position will be characterized by hips and knees at 90 degrees of flexion and a neutral ankle position with feet in full contact with the floor. During the 1 h of sitting, the participants will be instructed to avoid talking and to maintain the assigned sitting posture as much as possible. They will be able to make small adjustments if they feel too much discomfort. The Borg CR-10 scale will be given to the participants to complete after the one-hour sitting session.

4.Global perceived improvement

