### 2.13. Data Analysis

The normality of the distributions will be checked using the Shapiro–Wilk test. Data will be presented as mean ± SD where appropriate. For variables that do not meet the criteria of normality of distribution, data will be presented as medians and quartile ranges. Lavene’s test will be conducted to verify the homogeneity of variances. The chi-square test will be used for categorical variables. The Mann–Whitney U test will be used to compare the groups. The mixed-design ANOVA with two factors (intervention, time) will be used. Tukey’s post hoc test will be used for detailed comparisons. Effect sizes will be assessed by partial eta squared (ANOVA) or the Glass rank-biserial correlation coefficient (the Mann–Whitney U test). The significance level will be set at *p* < 0.05.

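### Three or four primary outcomes (the article contradicts itself), one unadjusted 0.05 and no rule across them: false-positive chance up to 14–19% if any one counts as success

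*Protocol article*

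**What the plan says.** **Which outcomes are primary.** The abstract gives three: "The primary outcome measures will be pain intensity, musculoskeletal discomfort, and functional disability". Section 2.9 brackets the same three: "Primary outcome measures (average pain intensity, functional disability, perceived musculoskeletal discomfort during prolonged sitting) will be collected at baseline". The rest of that sentence adds that global perceived improvement is rated after the intervention, without making its status clear. Section 2.10, headed as the primary outcomes, numbers four items; the last is "4.Global perceived improvement", scored on the GPE scale and dichotomised.

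**Which are secondary.** The abstract says "Secondary outcome measures will be satisfaction with the intervention and flexibility of the hamstring". Sections 2.9 and 2.11 give hamstring flexibility only. Table 2 lists five assessments, and satisfaction is not among them.

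**The Borg primary.** Section 2.10 has participants rate discomfort from 0 to 10 by region ("i.e., neck, shoulder, upper back, lower back, hip/thigh, and knee"). It names no total, maximum or lower-back score as the endpoint.

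**Testing.** Section 2.13 names chi-square and Mann–Whitney tests, and adds "The mixed-design ANOVA with two factors (intervention, time) will be used", with Tukey's test for follow-up comparisons. It then states "The significance level will be set at" p < 0.05. Nothing in it refers to several primary outcomes. Section 2.3 sizes the trial at 44 with d = 0.50, significance level 0.05 and power 0.85, and names neither an outcome nor a test.

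**The concern.** A reader cannot tell from the article which outcomes are primary, or what result would make the trial positive. Tukey's procedure does not help: it controls error among the cell comparisons within one ANOVA, not across pain, disability, discomfort and perceived effect. The sample size calculation gives no hint of a deciding outcome either, because it spends the whole 0.05 on an unnamed one.

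If each primary is tested at 0.05 and one significant result is enough to call the intervention effective, the error rate for that claim exceeds the stated 5%. The undefined Borg score adds a second looseness: six ratings are collected, and the article does not say which of them, or which combination, is the endpoint.

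**Working it through.** The article states no family-wise error rate, so there is no figure of its own to reproduce. The only stated level is 0.05 (section 2.13). I take it as two-sided, which the article does not say.

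**1. Number of tests, k**
- k = 3: pain (VAS), ODI and Borg CR-10 with one score (abstract; 2.9 bracket).
- k = 4: the same plus GPE (2.10).
- k = 9: VAS, ODI, GPE and six Borg regions. This is hypothetical, since no section states region-by-region testing.

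**2. Independent tests.** The chance of at least one false positive is 1 − 0.95^k:
- k = 3: 1 − 0.8574 = 14.3%
- k = 4: 1 − 0.8145 = 18.5%
- k = 9: 1 − 0.6302 = 37.0%

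**3. Correlated tests.** These outcomes come from the same people and are likely to be positively correlated. The article gives no correlations, so a range is assumed. Test statistics were simulated as z_j = √r·z₀ + √(1 − r)·e_j, with rejection when |z_j| > 1.96 (400,000 draws).

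| k | r = 0 (exact) | r = 0.3 | r = 0.5 | r = 0.7 | r = 0.9 |
|---|---|---|---|---|---|
| 3 | 14.3% | 13.7% | 12.6% | 10.9% | 8.3% |
| 4 | 18.5% | 17.4% | 15.5% | 13.0% | 9.3% |
| 9 (hypothetical) | 37.0% | 32.7% | 27.0% | 20.3% | 12.4% |

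The independence column is therefore a ceiling, not an estimate.

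**4. Favourable direction only.** Counting only false positives that favour the intervention, at r = 0.5, gives 6.3% (k = 3), 7.8% (k = 4) and 13.5% (k = 9). The benchmark for one two-sided test at 0.05 is 2.5%.

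**5. After the fix.** One named primary at 0.05 gives 5.0%. Splitting 0.05 over four (0.0125 each) gives 1 − 0.9875⁴ = 4.9% under independence.

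**6. Power cost of keeping several primaries.** As an illustration, assume a 2 × 2 mixed-ANOVA interaction with f = 0.25, pre–post correlation 0.5 and N = 44. The noncentrality is f²·N·m/(1 − ρ) = 0.0625 × 44 × 2 / 0.5 = 11.0, on 1 and 42 degrees of freedom.
- At 0.05: power 90%
- At 0.05/3 = 0.0167: 79%
- At 0.05/4 = 0.0125: 76%

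These inputs are assumed and do not reproduce the planned 44: at 85% power they need 38. They show the size of the loss, not the trial's actual power. Holm rejects whenever the equal split does, so 76% is a floor for any one of four outcomes under these assumptions.

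**The case against.** **This is a condensed article, and the analysis plan is not shown.** A multiplicity procedure, a success rule and the scoring of a multi-region scale may well be set out elsewhere. That stands against treating their absence alone as a fault. It does not touch what the article itself fixes: primary lists that disagree, a secondary outcome with no measurement, and one 0.05 for everything. A separate plan cannot make the abstract agree with section 2.10.

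**A reader might infer a false-positive chance of 19–37%.** The article does not support that as an estimate. Both ends assume independent outcomes, which is implausible here. The upper end also assumes that six regions are tested separately, whereas section 2.10 describes only how ratings are collected and section 2.13 names no regional test. The lower end ignores the two places that list three primaries, for which the ceiling is 14.3%.

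**A reader might also infer that the deciding outcome will be picked after the data are seen.** The article says the trial was prospectively registered, and that record is not at hand. What can be said is that this article does not by itself rule such a choice out.

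**The satisfaction mismatch adds nothing to the error rate.** True. It may be GPE under another name, and it is a matter of consistency only.

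**Conclusion.** The point holds in this form: the article gives three primary outcomes in two places and four in a third, lists a secondary outcome that is never measured, leaves the Borg primary without a defined score, and applies one unadjusted 0.05 with no rule across outcomes.

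If any single significant primary counts as success, the family-wise error is at most 14.3% (three) to 18.5% (four). At assumed correlations of 0.5 to 0.7 it is 10.9–12.6% for three and 13.0–15.5% for four, still more than twice 5%. The 37% figure (20–27% at the same correlations) applies only if the regions are also tested one by one.

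All of this rests on two-sided tests and on the any-one-succeeds reading. If every primary had to be significant, the error would not be inflated, but power would fall; the article does not say which rule applies. The contradiction between the lists is certain; the size of the error is conditional.

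**What to change.** 1. Give the same primary and secondary lists in the abstract and sections 2.9 to 2.11. Drop satisfaction, or state that it means GPE.
2. Name one primary outcome, tested at 0.05, and make the others secondary under Holm. If three or four must stay primary, apply Holm across them and say what counts as success.
3. Define one Borg score for testing, for example the lower-back rating, and report the other regions descriptively.
4. If VAS pain is to be the single primary, first reconcile its definition. Section 2.10 calls it average pain intensity but asks for the maximum over the last three months. That recall window is longer than the 8-week intervention, so a post-intervention rating would also cover time before treatment.
5. Tie the sample size statement to the named outcome and test.

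**Cost.** With one primary, the change is wording, and the outcomes moved down lose primary status. Keeping four under Holm makes the first threshold 0.0125 and can cost real power (about 90% to 76% in the illustration above), so the sample size would need another look. A single primary is the cheaper option.

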### 2.2. Study Population

The participants will be recruited according to the following inclusion criteria: (1) students of physical education; (2) age 18–25 years (18–25 years old); (3) with non-specific LBP; (4) with pain that has lasted at least 3 months; (5) without a history of spinal surgery; (6) no hamstring stretching exercises in the last 6 months; and (7) with hamstring muscle tightness.

The exclusion criteria are as follows: (1) specific LBP; (2) other criteria preventing participants from adequate participation in the study, such as pregnancyor menstrual pain; (3) leg length discrepancy over 1 cm; (4) previous spinal surgery; (5) presence of any contraindication to exercise; or (6) medically verified chronic back disorders.

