### 2.11. Secondary Outcome Measures

#### Flexibility of the Hamstrings

The flexibility of the hamstrings will be assessed using the single passive straight leg raise (SLR) test [31], measured in degrees by a goniometer. The SLR will be performed twice for each leg and the mean value of the two attempts will used for analysis [31]. A subject’s hamstring muscles will be considered tight (in a shortened position) if the SLR is ≤70° [32]. 

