### 2.12. Timeline of the Study

We designed the timeline of the study using the SPIRIT framework (Table 1). At enrollment, the purpose of the study and research procedures will be explained to the participants. The pre-screening will address the specific inclusion and exclusion criteria for the study, basic demographic data, and the frequency of LBP. Participants who meet the inclusion criteria will be invited to attend a baseline assessment (Table 2). All the tests will be performed during morning hours in the laboratory. 

At the baseline assessment session, participants will be requested to complete the VAS, ODI, and Borg CR-10 scale. After completion of the baseline assessment, participants will be randomly assigned to one of two groups (experimental or control), and simultaneous implementation of the exercise program will commence. After 8 weeks, all assessment measures for all participants will be repeated in the same way as the baseline measurements (Table 2).

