## Figures and Tables

**Table 1 jcm-13-04161-t001:** Exercises for active hamstring stretching with hip flexion mobilization.

1st part	
[figure not shown]	Foam roller massage. Starting position: sit on the mat with a straight spine, place the massage tool below the thigh, and roll the thigh between the buttock and the knee.
2nd part	
[figure not shown] [figure not shown]	Learning the pattern of flexion in the hip joints. Starting position: kneeling supported. Activation of the core muscles, and awareness of setting the lumbar spine in a neutral position. Moving the hips towards the heels, keeping the spine in a neutral position. Notes: keep the lower spine stable and the pelvis in an anterior tilt.
[figure not shown] [figure not shown]	Active stretching of hamstrings with the development of the habit of correct hip flexion and knee extension. Starting position: sit with a straight back, knees slightly bent. Flex hips and straighten knees. Hold. Knee flexion. Increase hip flexion and knee extension. Notes: keep the lower spine stable and the pelvis in an anterior tilt. The degree of flexion in the hips is adapted to the participant’s abilities.
[figure not shown] [figure not shown]	Active stretching of hamstrings with torso stabilization and correct hip flexion and extension; lumbar technique. Starting position: standing, facing the wall, legs slightly bent at the knees Hip flexion, then knee extension. Hold. Knee flexion. Hip flexion increase, knee extension. Notes: keep the lower spine stable and the pelvis in an anterior tilt. The degree of flexion in the hips is adapted to the participant’s abilities.

**Table 2 jcm-13-04161-t002:** SPIRIT table of enrollment, intervention, and assessment.

	Enrollment	Before Intervention	Randomization	Intervention
Timepoint	1st Month	2nd Month	2nd Month	3rd and 4th Months (8 Weeks)
Enrollment				
Eligibility pre-screening	+			
Informed consent	+			
Allocation			+	
Interventions				
Experimental and control group				+
Assessments				
Pain intensity		+		+
Functional disability		+		+
Perceived musculoskeletal discomfort		+		+
Global perceived improvement				+
Flexibility of the hamstring				+

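### Hamstring flexibility has no scheduled baseline, although eligibility needs a straight leg raise before randomisation and other sentences imply a repeated measure

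*Protocol article*

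**What the plan says.** Three specific places in the protocol article put hamstring flexibility after the intervention only.

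- Section 2.9: "The secondary outcome measure (flexibility of the hamstring) will be collected after the 8-week intervention". The sentence before it says that pain, disability and sitting discomfort "will be collected at baseline and immediately after the 8-week intervention, and the global perceived improvement will be assessed immediately after the 8-week intervention". The text thus separates outcomes measured twice from those measured once.
- Table 2: the row "Flexibility of the hamstring" has a single mark, in the intervention column, and is blank under the pre-intervention column. The rows for pain, disability and discomfort are marked in both.
- Section 2.12: at the baseline session, "participants will be requested to complete the VAS, ODI, and Borg CR-10 scale". SLR is not listed.

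Other places point the other way.

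- Section 2.7 says, without naming instruments, that outcomes are assessed at the start and after 8 weeks.
- Section 2.12 says that after 8 weeks "all assessment measures for all participants will be repeated in the same way as the baseline measurements".
- Section 2.2 admits only people "with hamstring muscle tightness". Section 2.11 defines tightness as an SLR of 70 degrees or less.
- Section 2.7 has a blinded physiotherapist "with five years of clinical experience will check the qualifying criteria".

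On procedure, section 2.11 says "The SLR will be performed twice for each leg and the mean value of the two attempts" is analysed. Section 2.13 lists a mixed-design ANOVA with intervention and time as factors, and a Mann–Whitney test between groups. It does not say which outcome each test serves.

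**The concern.** SLR is the only outcome that an examiner measures with an instrument. Pain, disability, discomfort and global perceived effect are all rated by participants, who are not blinded (section 2.5), and the Discussion concedes that self-report may be biased. SLR is also the direct check on whether the programme changed the muscle property it targets.

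Global perceived effect is also collected once, but it asks about change and can only be asked afterwards. No such reason applies to SLR. If the schedule is followed literally, a baseline not recorded before training starts cannot be recovered. The trial could then say whether the groups differ in flexibility at week 8, but not how far flexibility moved, and it would have no means of correcting a chance difference at entry in a sample of 44 to 48.

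**Working it through.** **1. The passages side by side.**

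| Place | SLR before randomisation? | SLR after 8 weeks? |
|---|---|---|
| 2.9 | not listed | yes |
| Table 2 | blank | yes |
| 2.12, baseline list | not listed | – |
| 2.12, follow-up sentence | implied by the word for repetition | yes |
| 2.7 | implied, SLR not named | implied |
| 2.2 criterion 7 with 2.11 | needed for eligibility | – |

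The three entries that name instruments or outcomes agree with one another. The two general sentences do not name SLR, and the follow-up sentence in 2.12 comes after a baseline list that omits it. That sentence cannot be fully literal either, since global perceived effect has no baseline to repeat. The eligibility rule implies that a reading exists, but no visit schedules it as an outcome assessment.

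**2. What one timepoint allows.** With a single SLR value per person, a model with a time factor has only one level of time, so neither the time effect nor the group-by-time interaction exists for SLR. A two-group comparison of the week-8 values can still be made.

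**3. What a baseline would add.** The plan gives no figure for SLR to reproduce. Inputs: total N = 44 and d = 0.50 from section 2.3, which does not tie that effect to SLR. Assumptions: 22 per arm (no ratio is stated), two-sided 0.05, and the correlation rho between baseline and week-8 SLR.

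Chance imbalance: the SD of the baseline mean difference is √(2/22) = 0.30 baseline SDs. A difference beyond 0.3 SD in either direction has probability 0.32. Unadjusted, a fraction rho of it carries into the week-8 comparison: 0.7 × 0.30 = 0.21 SD at rho = 0.7.

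Precision: residual variance under ANCOVA relative to week 8 alone is 1 − rho². The detectable difference scales with √(1 − rho²). Power is from the noncentral t with 42 degrees of freedom, ignoring the one degree of freedom spent on the covariate.

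| Analysis | 1 − rho² | Variance reduction | Power at d = 0.50 | Detectable at 85% power |
|---|---|---|---|---|
| Week 8 only | 1 | – | 0.37 | 0.92 SD |
| ANCOVA, rho = 0.5 | 0.75 | 25% | 0.46 | 0.80 SD |
| ANCOVA, rho = 0.7 | 0.51 | 49% | 0.62 | 0.66 SD |
| ANCOVA, rho = 0.8 | 0.36 | 64% | 0.77 | 0.55 SD |

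Selecting people at or below 70 degrees restricts the range of baseline SLR and may lower rho, so the upper rows are the safer guide.

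**The case against.** The strongest reply is that a baseline is probably intended. Sections 2.7 and 2.12 speak of outcomes at the start and repeated later, eligibility needs an SLR, and a blinded assessor checks eligibility. This is plausible, and it makes the point one of inconsistency rather than a clear decision to forgo a baseline. It does not remove it: three specific entries say otherwise, and if a baseline is intended, those entries are wrong.

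Several stronger readings are tempting, and the documents do not support them.

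- A reader might infer that the flexibility comparison is biased. It is not: randomisation protects a week-8 comparison, and the Mann–Whitney test in section 2.13 needs no baseline.
- A reader might infer that the planned analysis cannot be run. Section 2.13 does not assign the ANOVA to SLR; only the time-based analysis of SLR is lost.
- A reader might infer that the eligibility reading is discarded. Nothing says so; the article is silent on its use.
- A reader might infer that the two legs would be analysed as independent observations. Nothing proposes that, and how the legs are combined is detail commonly left to the analysis plan.

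It is also fair to say that the variance figures describe baseline adjustment in general, since every correlation is assumed, and that this is a secondary outcome. The three primary outcomes for which a baseline is meaningful have one.

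**Conclusion.** The point holds as a scheduling inconsistency with a real but limited cost. Followed as written, section 2.9, the baseline list in 2.12 and Table 2 leave the one examiner-measured outcome without a scheduled baseline. The between-group comparison at week 8 stays valid. Change within participants and the group-by-time effect are not estimable for SLR, chance imbalance at entry cannot be adjusted for, and precision is forgone: a quarter of the residual variance at rho = 0.5 and about half at 0.7.

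The loss of the change estimate follows from the schedule alone. The size of the precision loss rests on the assumed correlations, and the power figures also on equal arms and on borrowing d = 0.50 for this outcome. The conclusions on the primary outcomes are not affected. The correction should be made before the first participant starts training.

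**What to change.** Reconcile sections 2.7, 2.9, 2.12 and Table 2 so that SLR is listed at the pre-randomisation baseline assessment as well as after 8 weeks. State that both readings follow the two-attempt procedure of section 2.11 and are taken by the blinded assessor. State that groups are compared on post-intervention SLR by ANCOVA with baseline SLR as covariate.

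Say also which reading is the baseline. Table 2 puts eligibility pre-screening in month 1 and the pre-intervention assessment in month 2, and the article does not say that screening uses two attempts per leg. If the eligibility reading meets the procedure and is recorded, it can serve. If not, the cost is a few minutes of goniometry at a visit that already takes place.

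One caution on reporting: participants are selected for a low SLR, so regression to the mean can produce apparent improvement in both groups, most clearly if the qualifying reading is the baseline. Within-group change should not be interpreted alone. The baseline-adjusted difference between groups is the estimate to report.
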